## Abstract

**Background:**

Previous reports suggest that the attributes of frailty are multidimensional and include nutrition, cognition, mentality, and other aspects. We aim to develop an early warning model of frailty based on nutritional risk screening and apply the frailty early warning model in the clinic to screen high-risk patients and provide corresponding intervention target information.

**Methods:**

The proposed study includes two stages. In the first stage, we aim to develop a prediction model of frailty among older inpatients with nutritional risk. Study data were collected from a population-based aging cohort study in China. A prospective cohort study design will be used in the second stage of the study. We will recruit 266 older inpatients (age 65 years or older) with nutritional risk, and we will apply the frailty model in the clinic to explore the predictive ability of the model in participants, assess patients’ health outcomes with implementation of the frailty model, and compare the model with existing frailty assessment tools. Patients’ health outcomes will be measured at admission and at 30-day follow-up.

**Discussion:**

This project is the first to develop an early prediction model of frailty for older inpatients according to nutritional risk in a nationally representative sample of Chinese older inpatients of tertiary hospitals. The results will hopefully help to promote the development of more detailed frailty assessment tools according to nutritional risk, which may ultimately lead to reduced health care costs and improvement in independence and quality of life among geriatric patients.

**Trial registration:**

Chinese Clinical Trial Registry, ChiCTR1800017682, registered August 9, 2018; and ChiCTR2100044148, registered March 11, 2021.

**Supplementary Information:**

The online version contains supplementary material available at 10.1186/s12877-021-02396-3.

## Background

With the rapid rate of change in health services and the global economy, the world’s population is experiencing increased longevity, with increases in the segment of the global population comprising older adults [1–3]. Epidemiologic studies show that the proportion of adults aged 65 years and older is expected to exceed 16 % of the world’s population by 2050 [4], with 80 % living in low- and middle-income countries [5]. As the second largest economy worldwide, China currently has the world’s largest population with 1.44 billion people, which accounts for 19 % of the global population, and China is swiftly changing into an aging country [3, 6–8].

Undernutrition is a frequent and serious condition within the geriatric population admitted to the hospital, and nutritional status often deteriorates further during hospitalization [8–11]. Therefore, during hospital admission or at discharge, a large number of older patients will still be malnourished or at risk of malnutrition [12, 13]. As per the American Society for Parenteral and Enteral Nutrition recommendation, malnutrition refers to all deviations from adequate and optimal nutritional status, including energy undernutrition and overnutrition [14]. The term undernutrition is used to refer to generally poor nutritional status; however, because malnutrition often refers to undernutrition, both terms are widely used in a similar sense [15, 16]. Previous studies have reported that the prevalence of hospital malnutrition or malnutrition risk in older inpatients is high (30–50 %) [10, 17, 18]. Its negative impact on health substantially affects quality of life by increasing the risk of frailty, disability, and mortality [19, 20].

Poor nutritional status can increase the age-associated loss of muscle mass and strength and is therefore seen as having an important role in the development of sarcopenia and subsequent physical impairment [21], which both represent substantial elements of the frailty syndrome [16, 22, 23]. Boulos et al. conducted a cross-sectional study among 1200 community–dwelling older adults living in a rural setting of Lebanon to examine the association between malnutrition and frailty. Those authors reported that both malnutrition and malnutrition risk were related to a significantly increased risk of frailty (odds ratio [OR] 3.72, 95 % confidence interval [CI] 1.40 to 9.94 and OR 3.66, 95 % CI 2.32 to 5.76, respectively) [9].

Frailty is a complex, age-related clinical condition characterized by a decline in physiological capacity across several organ systems, and it is a state of increased vulnerability to stress [9, 22, 24]. However, older adults with frailty have an increased likelihood of unmet care needs, falls and fractures, hospital readmissions, increased length and cost of hospital stay, lower quality of life, iatrogenic complications, and early mortality [10, 24]. This increased risk of adverse clinical outcomes can occur even without the presence of comorbidities [24, 25].

The investigation of frailty has attracted enormous scientific interest in the past few years as it affects multiple domains of human functioning, including nutritional status, cognitive function, gait, mobility, balance, muscle strength, endurance, and activities of daily living (ADL) [26]. Additionally, previous reports have suggested that the attributes of frailty are multidimensional and that its definition should comprise nutrition, cognition, mentality, and other aspects [27–30]. Identification is a critical step in the intervention or management of frailty [24, 29, 30]. Both the cycle of frailty model [22] and the integral conceptual frailty model [31] include nutrition as a factor to explain frailty. However, undernutrition is considered a sub-factor in physical frailty in the integral conceptual frailty model and a predisposing factor for frailty in the cycle of frailty model [22]. Previous studies have mainly investigated the relationship between undernutrition and frailty [9, 21, 32, 33], but none have reported the degree of influence on frailty according to nutritional risk, despite nutritional risk being a modifiable variable.

Using the current study protocol, in the first stage of this study, we used data from a cohort study to develop an early warning model of frailty based on nutritional risk screening. In the second stage of the study, we report the prevalence of frailty among older inpatients with nutritional risk and apply the frailty early warning model in the clinic to screen high-risk patients and provide corresponding intervention target information.

## Methods

### Study design

The study includes two stages. In the first stage, we aim to develop a prediction model of frailty among older inpatients with nutritional risk. Study data were collected from a population-based aging cohort study in China. A prospective cohort study design will be used in the second stage of the study. We will apply the frailty model in the clinic to explore the predictive ability of the model in participants, assess patients’ health outcomes with implementation of the frailty model, and compare the model with existing frailty assessment tools.

### Developing the frailty model according to nutritional risk

#### Data used for modeling

The data used for development of the prediction model were derived from an ongoing, prospective large-scale cohort study among older Chinese inpatients at tertiary hospitals (Chinese Clinical Trial Registry Number: ChiCTR1800017682). In the present study, we used baseline survey data collected from October 2018 to February 2019; details can be found elsewhere [3, 10]. Briefly, this study is a nationwide survey that provides representative data for the investigation of geriatric factors, such as nutritional status, cognition, or physical activity, in hospitalized older individuals aged ≥ 65 years nationwide. Eligible participants are recruited from five provinces and one municipality in China (southwest: Sichuan Province; northeast: Heilongjiang Province; south–central: Hubei Province; northern: Beijing municipality/city; northwest: Qinghai Province; eastern: Zhejiang Province). All eligible older individuals are continuously enrolled. Surveys are administered by trained nurse interviewers using a structured questionnaire. The interview language used is standard Mandarin/Putonghua. Proxy respondents, usually a spouse or other legal guardian, are interviewed if the patient is unable to answer the questions themselves.

#### Feasibility of recruitment and sample size

In the first stage, for the sample size required for modeling, we referred to the method of estimating sample size for multivariate logistic regression. For the categories with a smaller proportion of the outcome variables, the sample size should be at least 10 times the number of independent variables. There are two categories of dependent variables in this study (no frailty and frailty), and 20 important independent variables were initially estimated. Therefore, the sample size of the intervention group in this study is at least 200 patients. According to the literature data, the incidence of frailty in the older population with nutritional risk is approximately 26.5–54 % [18, 32, 34, 35]. Taking into account an expected incidence of 40 % and loss to follow-up of 10–20 %, we aim to include 600 patients. As for the total sample size, with reference to logistic regression modeling requirements, the modeling sample size is approximately two-thirds of the total sample size and the model verification sample size is approximately one-third of the total sample size. The total sample size is calculated to be at least 900 patients, of which at least 300 patients will be used for model verification.

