#### Population and inclusion and exclusion criteria

In the first stage of modeling, participants must meet the following criteria: having no frailty according to the FRAIL (Fatigue, Resistance, Ambulation, Illnesses, & Loss of Weight) scale (scores from 0 to 2), malnourished or at risk of malnutrition according to the Mini-Nutritional Assessment-Short Form (MNA-SF; scores range from 0 to 11), and written informed consent provided by patients enrolled in this study.

Exclusion criterion were as follows: patients with frailty at the time of enrollment; patients who are persistently unconsciousness or unable to provide informed consent for participation, or their caregivers were unable to provide effective information; patients who were initially admitted to the intensive care unit (ICU) [13]; patients with anorexia nervosa, acute pancreatitis, acute liver failure, cystic fibrosis, stem cell transplantation, severe chronic gastrointestinal diseases, acute infectious diseases or chronic wasting diseases at enrollment; and patients who were lost to follow-up or had died at the 30-day of follow-up. A total of 3027 patients were enrolled in the current study.

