#### Definition of covariates

Potentially associated factors of frailty in the models included [16, 36–43] age, sex, ethnicity, education level, marital status, body mass index (BMI), living alone, living conditions, smoking, alcohol consumption, falling accidents in the past 12 months, immobilization for more than 4 weeks, polypharmacy, fatigue, resistance (ability to climb stairs), ambulation (ability to walk 100 m), illnesses (> 5), loss of more than 5 % body weight, nutritional risk, ADL, instrumental ADL, depression, cognitive function, handgrip strength, vision, hearing, sleeping, urinary function, and defecation function.

Age was grouped as 65–74 years old, 75–85 years old, and 85 years old and above. Ethnicity was categorized as Han and ethnic minorities. Education level was categorized as illiterate, primary school, junior high school, and high school and above. Marital status was categorized as married and divorced or widowed. Living alone was categorized as living alone or not living alone [40]. Living conditions was classified as living in a building with an elevator, a building without an elevator, or a bungalow. Polypharmacy was categorized as 0, 1–2, 3–4, 5–6, and more than 7 [16].

BMI was calculated as body weight divided by height (in meters) squared (kg/m^2^) [18] and was used to classify patients into groups of < 19 kg/m^2^, 19 to < 21 kg/m^2^, 21 to < 23 kg/m^2^, and ≥ 23 kg/m^2^. Participants’ weight in kg was measured to the nearest 0.1 kg using a digital electronic chair scale, and height (in cm) was measured to the nearest 1 mm using a stadiometer. Study participants were weighed while wearing light clothing and no shoes.

We referred to the FRAIL scale [38, 44], such as the items of fatigue, resistance (ability to climb stairs), ambulation (ability to walk 100 m), illnesses (> 5), and loss of more than 5 % body weight, which has been validated in Chinese older adults [45].

Nutritional risk was measured using the MNA-SF, a six-item scale with scores ranging from 0 to 14 points [19]. Patients were categorized into patients at risk of malnutrition (8–11 points) or malnourished (0–7 points) [39]. The MNA-SF has been validated in the Chinese population and has excellent test characteristics [10, 46].

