#### Statistical considerations

Descriptive results are expressed as mean and standard deviation (SD) or as number and percentage. Bivariate analyses will be performed using the χ^2^ test or Fisher’s exact test for qualitative variables and the Student *t-*test, analysis of variance (ANOVA), or Kruskal–Wallis test for quantitative variables. Logistic regression analysis will apply in variable selection and we used an entry criterion of *P* < 0.05. The data set will be divided into a training (70 %) and verification (30 %) set using random sampling. We will establish a frailty prediction model using the modeling data set, and discrimination will be expressed using area under the receiver operating curve and the Hosmer–Lemeshow test to evaluate goodness of fit [59]. As for internal validation, we will use a bootstrap technique with 1000 resamples from the training data set. The verification data set will be used for external verification, and its effectiveness evaluated according to accuracy and area under the receiver operating curve. All statistical analysis will be performed using Stata version 14 for Windows (Stata Corp, College Station, TX, USA). A *P* value of less than 0.05 will be considered statistically significant.

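### The Stage 1 sample size is justified for 20 predictors, but 29 candidates are listed and the 40% event rate is not shown to apply to a cohort non-frail at entry

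*Protocol article*

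**What the plan says.** All references are to the Stage 1 part of the protocol article (Developing the frailty model according to nutritional risk).

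- **Feasibility of recruitment and sample size** sets the rule for the smaller outcome category: "the sample size should be at least 10 times the number of independent variables". It then says that "20 important independent variables were initially estimated" and concludes: "Therefore, the sample size of the intervention group in this study is at least 200 patients". The study has no intervention group at this stage, so I read this as the frail category.
- The same section says that "the incidence of frailty in the older population with nutritional risk is approximately 26.5–54" per cent, takes 40% as the expected value, allows 10–20% loss to follow-up, and arrives at 600 for modelling. Taking modelling as two-thirds of the total gives at least 900.
- **Definition of covariates** introduces its list with "Potentially associated factors of frailty in the models included". Age, education, BMI, living conditions and polypharmacy are given three or more levels.
- **Population and inclusion and exclusion criteria** admits only patients with a FRAIL score of 0–2, excludes those lost or dead at 30 days, and states: "A total of 3027 patients were enrolled in the current study".
- **Statistical considerations** says "Logistic regression analysis will apply in variable selection and we used an entry criterion of" P < 0.05. It plans a 70/30 split and a bootstrap of 1000 resamples from the training set.

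**The concern.** An events-per-variable rule is meant to limit overfitting. When predictors are chosen from the data, the count that matters is the number of candidates examined, because each one is a chance for noise to enter the model. The number retained does not measure this. The plan sizes for 20 but offers 29 to the selection step.

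The second input is the event rate. The 40% is quoted for older people with nutritional risk in general. The modelling cohort is restricted to those not yet frail, so the event can only be frailty that develops after entry. Nothing in the section connects 40% to that event or gives it a time horizon.

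At stake is whether a reader can rely on the stated protection. With too few events per candidate, P-value selection tends to give coefficients that are too large and predicted risks that are too extreme. This model is to be carried into a clinic in Stage 2.

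**Working it through.** **1. Reproduce the plan's figure.**
- Events: 10 × 20 = 200.
- Evaluable patients: 200 / 0.40 = 500.
- Loss to follow-up: 500 / (1 − d) gives 556 at d = 10% and 625 at d = 20%. The stated 600 is 500 × 1.2, or d = 1 − 500/600 = 16.7%, inside the stated range.
- Total: 600 × 3/2 = 900.

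The arithmetic is sound on its own inputs.

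**2. Count the candidates in Definition of covariates.**
- Age, sex, ethnicity, education, marital status, BMI, living alone, living conditions: 8
- Smoking, alcohol: 2
- Falls, immobilisation, polypharmacy: 3
- The five FRAIL items: 5
- Nutritional risk, ADL, instrumental ADL, depression, cognition, grip strength: 6
- Vision, hearing, sleep, urinary function, defecation: 5

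Total: 29.

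**3. Apply the plan's rule to 29, other inputs unchanged.**
- Events: 10 × 29 = 290.
- Evaluable: 290 / 0.40 = 725.
- Modelling: 725 / 0.9 = 806 to 725 / 0.8 = 907.
- Total: 806 × 1.5 = 1209 to 907 × 1.5 = 1361.

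**4. What 600 modelling patients deliver** (size of the smaller category, for 10% and 20% loss).

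| Frailty rate | Smaller category | Per variable, 20 | Per variable, 29 |
|---|---|---|---|
| 40% (plan) | 600 × 0.9 × 0.40 = 216; 600 × 0.8 × 0.40 = 192 | 10.8; 9.6 | 7.4; 6.6 |
| 26.5% (plan's low end) | 143; 127 | 7.2; 6.4 | 4.9; 4.4 |
| 54% (plan's high end; non-frail is smaller) | 248; 221 | 12.4; 11.0 | 8.6; 7.6 |

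No rate rescues 600 with the stated loss. The evaluable number is 540 or 480, so the smaller category cannot exceed 270 or 240, which is below 290.

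**5. What the 3027 enrolled deliver.** The section gives 3027 together with the exclusion of patients lost or dead at 30 days, so I deduct no further loss. The training set is 3027 × 0.70 ≈ 2119.
- At 40%: 848 events, 848 / 29 = 29.2 per candidate.
- At 26.5%: 562 events, 562 / 29 = 19.4 per candidate.
- Incidence needed for ten per candidate: 290 / 2119 = 13.7%.

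**6. Sensitivity to coding (assumption).** If the five multi-level factors are dummy-coded and the other 24 take one coefficient each, the count is 24 + 2 (age) + 3 (education) + 3 (BMI) + 2 (living conditions) + 4 (polypharmacy) = 38. Ten per parameter then needs 380 / 2119 = 17.9%.

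**7. The event rate.** The cited range and the 40% describe a population with nutritional risk, and the cohort excludes those already frail. The document gives no incidence of new frailty in such patients, so the size of any discrepancy cannot be computed.

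**The case against.** The strongest reply is that 900 is a minimum and the data set holds 3027. On the plan's own range of 26.5–40%, the training set gives 19 to 29 events per candidate, well above ten. This stands. A reader might infer from the shortfall at 600 that the fitted model will be overfitted, and the document does not support that.

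It may also be said that 20 means the variables expected to survive selection. This does not help, because selection at P < 0.05 runs over the candidates.

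Three further points limit the claim:
- **Coding.** The rule counts variables, and several multi-level factors are ordered groups that could enter as single terms. A reader might take 38 parameters as a floor, but it depends on dummy coding that the plan does not state.
- **Event rate.** It is tempting to say that 40% must be a prevalence and that true incidence is, say, 5% or 10%. The document gives neither figure and the cited sources are not at hand. Stage 1 also gives no explicit time point for the outcome; 30 days appears there only in an exclusion criterion.
- **Safeguards.** The bootstrap and the 30% verification set are real checks on optimism. They detect it but do not remove it from the coefficients, and the text does not say that selection is repeated within each resample.

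**Conclusion.** The written justification is wrong as it stands. By the plan's own rule, the listed candidates need 290 events rather than 200. The stated 600 delivers 192–216 on the plan's rate and loss, which is 6.6–7.4 per candidate, and cannot reach 290 at any rate once 10–20% are lost. The consistent figures are about 806–907 for modelling and 1209–1361 in total. This part rests only on the count of 29 and the plan's inputs.

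The 40% is not shown to apply to new frailty in patients who are not frail at entry. It is reasonable to expect a lower figure, but its size is unknown.

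Neither point shows that the model actually fitted is too small. With about 2119 in the training set, ten per candidate holds if incidence is at least 13.7%, or 17.9% per parameter under the dummy-coding assumption, and fails below that. The document does not report the event count, so the question stays open. The error is in the inputs and not in the calculation from them.

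**What to change.** Rewrite the Stage 1 sample-size paragraph from what exists:

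- the 29 listed candidates;
- the 3027 patients available;
- the observed number of new-frailty events in the training set;
- events per candidate variable, and per parameter once the coding of multi-level factors is fixed.

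State plainly that the 40% was not derived for patients non-frail at entry.

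In Statistical considerations, say that the P < 0.05 selection is repeated inside each of the 1000 bootstrap resamples already planned, and that the resulting shrinkage is applied to the coefficients. A change to ridge or LASSO would be a modelling preference and is not needed to correct this error.

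The cost is one rewritten paragraph, one added method line and slightly more analysis work. The stated events-per-variable justification becomes less favourable. No extra patients are needed.

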#### Population and inclusion and exclusion criteria

In the first stage of modeling, participants must meet the following criteria: having no frailty according to the FRAIL (Fatigue, Resistance, Ambulation, Illnesses, & Loss of Weight) scale (scores from 0 to 2), malnourished or at risk of malnutrition according to the Mini-Nutritional Assessment-Short Form (MNA-SF; scores range from 0 to 11), and written informed consent provided by patients enrolled in this study.

Exclusion criterion were as follows: patients with frailty at the time of enrollment; patients who are persistently unconsciousness or unable to provide informed consent for participation, or their caregivers were unable to provide effective information; patients who were initially admitted to the intensive care unit (ICU) [13]; patients with anorexia nervosa, acute pancreatitis, acute liver failure, cystic fibrosis, stem cell transplantation, severe chronic gastrointestinal diseases, acute infectious diseases or chronic wasting diseases at enrollment; and patients who were lost to follow-up or had died at the 30-day of follow-up. A total of 3027 patients were enrolled in the current study.

